#### Interim analysis

A formal interim analysis will be performed after occurrence of the first four primary outcomes. The data safety monitoring board (DSMB) will assess the results and it will be determined whether the occurrence of the primary outcome was related to the index suspected bacterial infection or more likely to be an unrelated infection. The outcome of that interim analysis will determine after how many primary outcomes the next interim analysis will be performed. When more than 75% of related cases occur in the intervention arm in two consecutive interim analyses, the study will be stopped prematurely.

Secondary outcomes and their statistical analyses are described below.

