### Power calculation

Relapse of proven GBS infection is estimated to occur in 0%–8% of patients, but may be caused by a different strain.^17^ Two epidemiological studies estimated the recurrence rate to be 1% in proven bacterial neonatal infections.^18 19^ The current study focuses on probable infections (in which the recurrence rate is likely even lower, although evidence for this is lacking). The incidence of community-acquired late-onset sepsis in otherwise healthy neonates is low (~0.28 per 1000 live births).^20^ Therefore, we assume a 1% infection rate (including new non-related infections) in both groups. Based on a non-inferiority margin of 3% (minimum success rate 96%), 2×231 patients are needed for a power of 90% using a one-sided alpha of 0.025. Because of the first 30 patients undergoing PK measurements and uncertainty about the PK values, and potential drop-out or withdrawal (estimated approximately 5%–10%), we will include 2×275 neonates (total=550). A post hoc report on the design effect will be included.

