## Discussion/conclusion

Prolonged hospitalisation for intravenous therapy is still common practice in high-income societies when neonatal bacterial infection cannot be ruled out despite negative cultures. In-hospital treatment has a high impact on both patient and parents since prolonged hospitalisation often leads to infant–parent separation. Initiatives to prevent separation through the reduction of admission days are of increasing interest. The additional value of other biomarkers besides CRP, such as PCT, in order to rule out bacterial infection has been evaluated. A recent study showed that using PCT values as guidance for antibiotic therapy in neonates with a suspected bacterial infection leads to a reduction in days on therapy and hospitalisation. However, when the infection could not be ruled out, as is the case in infants with a probable infection, therapy was still continued intravenously for 7 days.^26^ We propose the first randomised controlled trial in a high-resource setting with a non-inferiority study design in order to demonstrate that oral antibiotic switch therapy is as effective as intravenous treatment in neonates with a probable bacterial infection. Furthermore, we will be the first to perform PK/PD analysis on oral amoxicillin/clavulanic acid on a large sample size. Once proven that serum concentrations following oral administration are adequate, and non-inferiority of oral switch has been proven, oral switch therapy could potentially be expanded to clinically well infants with a proven infection.

This study has some limitations, the most important limitation relating to the primary outcome assessment. As mentioned in the methods section, only neonates with a probable bacterial infection will be included. It is impossible to state whether or not a second infection is a reinfection or that it is caused by a different pathogen. We, therefore, developed a list of recommended diagnostics that should be determined when a participant returns with signs of a possible infection. Those results can be used for correct and uniform assessment of the event and will help differentiating between a true bacterial infection, a probable bacterial infection or a viral infection.

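### The stopping rule counts related cases, which the protocol says cannot be established, and lets an interim result set the next look, so its error rates are undefined

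*Protocol article*

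**What the plan says.** The Interim analysis section places the first formal look at four primary outcomes. The DSMB assesses the results, and each event is judged either related to the index infection or more likely unrelated. On timing: "The outcome of that interim analysis will determine after how many primary outcomes the next interim analysis will be performed". The stopping criterion is: "When more than 75% of related cases occur in the intervention arm in two consecutive interim analyses, the study will be stopped prematurely".

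Four other places bear on this:

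- The Discussion says of a later episode: "It is impossible to state whether or not a second infection is a reinfection or that it is caused by a different pathogen". The Strengths and limitations box makes the same point and gives sterile first cultures as the reason.
- The section on molecular techniques says sequencing will be run in batches, with results not immediately available to the DSMB when a (re)infection occurs.
- The Randomisation and blinding section makes the trial open label and blinds only the investigators who do the statistical analysis.
- The Power calculation says "we assume a 1% infection rate (including new non-related infections) in both groups". It finds that "2×231 patients are needed for a power of 90% using a one-sided alpha of 0.025" and then states "we will include 2×275 neonates (total=550".

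**The concern.** The rule has two weak parts.

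The first is what it counts. Relatedness decides which of a handful of events enter the stopping fraction, and the article itself says the distinction cannot be made. The judgement is made in an open-label trial, and the article states no masking for it. If knowledge of the arm influences it, the fraction is biased. The rule also counts something different from the powered endpoint, which includes unrelated infections.

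The second is when it looks. The next look depends on the result of the one before, so the chance of stopping under harm, or under no difference, cannot be worked out from the rule as written.

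This is the only formal stopping criterion that the article states, and the participants are newborns. A DSMB applying it would not know how likely it is to miss real harm or to stop a sound trial.

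**Working it through.** **Inputs.** From the Power calculation: 1% in each arm, margin 3 percentage points, one-sided alpha 0.025, power 90%, 231 evaluable and 275 enrolled per arm. From the Interim analysis section: first look at 4 events; more than 75% of related cases in the oral arm at two consecutive looks. Assumed, because not stated: spacing of later looks, cumulative counting, and the share of cases judged related.

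**1. The plan's own sample size.** n per arm = 2 × 0.01 × 0.99 × (1.960 + 1.282)² / 0.03² = 231.16. The stated 231 is reproduced, apart from rounding.

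**2. Chance of reaching a second look at the planned rate.** Expected events: 550 × 0.01 = 5.5. With X ~ Binomial(N, 0.01), the exact tails are:

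| Look placed at | N = 550 | N = 462 |
|---|---|---|
| 4 events (first look) | 80% | 68% |
| 5 events | 64% | 49% |
| 6 events | 47% | 32% |
| 8 events | 19% | 10% |

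**3. The same under harm at the margin.** At 4% v 1% with 275 per arm, expected events are 275 × 0.05 = 13.75. Convolving the two binomials gives P(at least 8 events) = 97%.

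**4. How often the written rule stops the trial.** Trials were simulated with 275 per arm, random event order, the first look at 4 events, cumulative counts and all cases related:

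| Spacing after the first look | Stops at 4% v 1% | Stops at 1% v 1% |
|---|---|---|
| every 4 events | 46% | 0.4% |
| every 2 events | 65% | 2.5% |
| every event | 79% | 7% |

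The smallest figure can be checked by hand. With no difference, the first look needs 4 of 4 (1/16) and the second needs at least 7 of 8, so at least 3 of the next 4 (5/16). The eighth event is reached in 19% of trials. The product, 1/16 × 5/16 × 0.19, is 0.0037; looks at 12 events or later add little.

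Counting only events since the last look changes the detection figures to about 27% (every 4) and 77% (every 2).

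**5. Sensitivity to the relatedness judgement.**

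- If half of all cases are judged related, whatever the arm, false stops with cumulative looks every 2 events rise from about 2.5% to 7%.
- If 70% of oral-arm cases but only 30% of control cases were judged related (an assumption chosen to show the effect of unmasked judgement), they rise to about 17%.

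**The case against.** **Relatedness.** The Interim analysis section asks only which explanation is more likely, not for proof, and the Discussion describes recommended diagnostics for uniform assessment. A reader might infer that the adjudication cannot be done at all; the text does not go that far. What stands is narrower. The diagnostics are described as separating true bacterial, probable bacterial and viral infection, not as linking an episode to the first one. A likelihood judgement with little to support it still decides the count.

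**Too few events.** A reader might infer that a second look will seldom be reached. That depends on a spacing the article does not fix: 19% fits a look at 8 events, but a look at 5 is reached in 64% of trials. These figures also assume equal 1% rates, where a harm rule ought not to stop the trial. Under harm at the margin, 8 events are reached in 97%.

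**Threshold and the two-look requirement.** Four of four oral-arm events cannot stop the trial at the first look, and one related case in that arm can raise a flag. Neither shows an error. One flag does not stop the trial, since two in a row are needed. An alternative such as an exact binomial boundary (one-sided p ≤ 0.035 at each event) also cannot stop at 4 of 4, where p = 0.5⁴ = 0.0625. It performs much like the written rule with looks every 2 events: about 68% v 65% detection, with about 2% false stops each.

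**Other safeguards and documents.** The Safety consideration section adds yearly DSMB review and interim analyses when necessary, so the rule is not the only oversight. A minimum case count, the counting basis and operating characteristics may sit in a charter or full protocol, and their absence from an article is no fault. Result-dependent timing is different: the article states it outright.

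**Conclusion.** The concern holds in two respects. The stopping criterion depends on a distinction that the article elsewhere says cannot be established, with sequencing results unavailable to the DSMB at the time and no masking stated. The next look is set by an interim result, so the rule has no defined operating characteristics.

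Its size is the spread that the same sentence permits: about 46% to 79% stops at 4% v 1%, and about 0.4% to 7% at 1% v 1%. This rests on cumulative counts, all cases related, and spacings from every four events to every event. Differential judgement by arm could add to false stops; the 17% above illustrates this and is not a prediction.

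The documents do not support a claim that the rule fails for lack of events, or that the 75% threshold or the two-look requirement is a mistake. Those are choices for the sponsor and DSMB.

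**What to change.** - Reconcile the Interim analysis section with the Strengths and limitations box, the molecular techniques section and the Discussion on whether relatedness can be judged, and on what evidence.
- Apply the stopping criterion to all primary outcome events by arm, the events the trial is powered on.
- Fix the look schedule in advance, independent of any interim result, and say whether counts are cumulative.
- State the resulting probability of a false stop at 1% v 1% and of stopping at 4% v 1%.
- Keep relatedness as a supportive assessment, made on case material masked to arm.

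The cost is protocol and charter wording, and possibly a few more short DSMB reviews. Counting all events also brings some dilution: unrelated infections, if evenly spread, pull the oral-arm share towards one half. The stated probabilities would show whether that is acceptable. Whether to keep the two-look requirement, and which boundary to use, can be settled by the sponsor and DSMB once those probabilities are known.

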### Secondary outcomes

#### Pharmacokinetics

Blood samples of the first 30 patients treated with oral antibiotics (intervention arm) will be analysed in order to confirm that plasma concentrations are within target range and to endorse safety and dosing of the investigated product. It is thought that time above the minimal inhibitory concentration (MIC) should be at least 40%–50% in order for treatment with penicillins to be adequate.^21^ Therefore, T>MIC should be at least 50% in 90% of the cases to be considered adequate, otherwise dosing needs to be adjusted. A target MIC of 8 mg/L is chosen for amoxicillin since this is the clinical breakpoint for *Escherichia coli* susceptibility defined by the European Committee on Antimicrobial Susceptibility (Eucast).^22^ In a later stage, sampling will be continued in order to develop a pharmacokinetic/pharmacodynamic (PK/PD) model and to perform a population PK analysis. For the first 30 patients, two blood samples (0.5 mL whole blood) will be collected; the first sample 4–6 hours after the first or second dose, the second sample 6–8 hours after the second or third dose of oral suspension. In a subset of patients, we will collect two samples following the same administration in order to calculate an area under the curve. After the first analysis on samples from 30 patients, sampling will be continued through the collection of a single blood sample per patient. Samples will be handled within 1 hour after collection by the local laboratory. The sample will be centrifuged at 3000 rpm for 10 min and the recovered plasma will be stored at −80°C. Once enough samples have been collected for analysis, they will be shipped to the Erasmus MC for analysis. Serum concentrations of both amoxicillin and clavulanic acid will be measured. For each measurement, 50 μL of plasma is needed. Analysis will be performed batchwise combining both liquid chromatography and mass spectrometry. Analysis will be performed by descriptive statistics and by using non-linear mixed-effects modelling including variables such as timing of blood drawing, timing of last meal, patient weight, centre.

#### Molecular techniques for bacterial detection

Left over material of blood culture before initiation of antibiotic treatment will be stored at −80°C. Molecular analysis will be performed using next generation sequencing (NGS) methods, evaluating the additional yield of those techniques on bacterial detection compared with blood culture. Analysis will be performed batchwise, meaning that the additional value will be determined afterwards and that results will not be immediately available for the treating clinician nor for the DSMB in case of a (re)infection. However, results will be available at the end of the study and will be analysed in regard to primary outcomes that have occurred during the course of the study. The analysis of the NGS will initially be exploratory. If substantial differences are noted in the yield of recovered organisms from NGS compared with the blood culture, further analysis may be undertaken, exploring the relationship with clinical data such as inflammatory parameters and clinical illness. In that instance, mixed models will be used, and adjustments will be made for centre.

#### Gut microbiome

Microbiome alterations following antibiotic therapy, both in the intervention and control group, will be evaluated in 80 participants from four centres. Faecal samples will be collected at five different moments in the first year of life (around day 7, 30, 90, 180 and day 365) from neonates born vaginally. Samples will be collected from the diaper and immediately stored at −20°C in a special box placed in the home freezer. Parents will receive a notification at each sampling moment including a questionnaire regarding episodes of antibiotic treatment, type of feeding, daycare attendance and the presence of siblings at home. After 365 days, all samples will shipped to the central research locations and stored at −80°C until analysis in a specialised facility using high throughput sequencing targeted at the bacterial 16S rRNA locus. Alpha diversity of all samples will be calculated by the Shannon index. We will identify time points in which the alpha diversity and relative abundances in operational taxonomical units differ between the infants with intravenous treatment and infants with intravenous-to-oral switch with a smoothing spline analysis of variance. Moreover, differences in the relative abundances of the genera will be tested with a linear mixed-effect model with correction for the variables of other antibiotic use, feeding type, day care attendance/sibling and centre.

#### Cost-effectiveness analysis

Following a superiority design, the cost-effectiveness analysis (CEA) will make a comparison between the intervention and the control group by identifying, measuring and valuing the costs and patient outcomes of both treatment strategies.

Following established methods for economic evaluations and costing studies in healthcare, both medical costs and non-medical costs (ie, costs of productivity losses) will be analysed for both study groups.^23 24^ Total medical costs over the 28-day follow-up period will be calculated, including costs of intravenous antibiotics, costs of oral antibiotics, laboratory costs and costs of hospitalisation days. In regard to readmission costs, only costs of a readmission for a bacterial (re) infection, as defined in the outcome measures section, will be added to the analysis. Resource consumption will be derived from electronic hospital databases. Unit prices will be calculated using real economic cost prices or using standard cost prices for health economic evaluations. Unit prices will be multiplied by the quantities for each resource used, and then summed over the separate types of resource to give a total cost per patient. Then, productivity costs in the patients’ parents/caregivers, consisting of productivity losses regarding both paid and unpaid work, will be analysed (ignoring prearranged, regular maternity and paternity leave). These costs will be measured using the institute of Medical Technology Assessment Productivity Cost Questionnaire,^25^ completed by the parents during the scheduled follow-up as described above. The productivity costs will be valued following the friction cost method. Briefly, the valuation of paid work will be based on average hourly labour costs per paid employee, whereas that of unpaid work will be based on the replacement costs for household work. Finally, all costs will be summated for each individual patient.

Regarding the patient outcomes, the CEA will look at the number of bacterial (re) infections within 28 days after finishing of antimicrobial therapy. Building on the data on costs and outcomes described above, a cost-effectiveness ratio will be calculated (the final endpoint of the CEA). This ratio will be expressed as incremental costs per bacterial (re)infection avoided. Otherwise, the CEA will focus on dominance of one treatment over the other with respect to lower cost and greater effect. Analysis of uncertainty in the estimation of the incremental cost-effectiveness ratio is illustrated through a cost-effectiveness plane (via bootstrapping). Where relevant, sensitivity analysis will be performed to assess the robustness of the analysis to certain assumptions.

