### Follow-up

Neonates will only be discharged from the hospital if they have shown to tolerate the oral antibiotic treatment for at least two doses and are clinically well. Parents will be interviewed by telephone on the first day after discharge and on day 14 after initiation of antibiotic therapy by the local study investigator or research nurse. The local investigator will assess antibiotic intake, signs of infection, side effects and events. In addition, parents will receive a survey on day 7 and day 21 with questions regarding possible signs of infection, side effects, QOL, loss of productivity, and cost-effectiveness and demographic data (maternal, paternal age, highest level of education, socioeconomic status and siblings). All surveys are available as online supplementary material. The primary outcome of the study is assessed 28 days after treatment completion, when the patient will be seen by the local investigator or research nurse for a final visit at the outpatient department. Parents of participants in the oral treatment group will be asked to return the bottle with remaining antibiotic suspension in order to evaluate medication adherence through measurement of the remaining amount of medication present in the bottle. Follow-up of neonates in the control group will be identical.

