#### Quality of life

To get an impression of the impact of an early intravenous-to-oral antibiotic switch on the QoL of both parents and their child, parents will be asked to fill in a questionnaire on day 7 and day 21. Since there is no validated QoL instrument for neonates <1 month, we developed a questionnaire ourselves that collects information on total admission days and readmission rate, symptoms, side effects, amount of intravenous cannulas inserted during admission, sleep quality of the patient, number of medical visits and medication use in the first month, feeding and breastfeeding success rate and parents’ satisfaction. Outcome reporting will be mainly descriptive, if a trend is observed for some of the questions, mixed-effect models can be used to further explore the effect of treatment and centre.

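### The cost-effectiveness analysis costs only readmissions for bacterial (re)infection, which may favour the oral arm, and its productivity surveys end about 14 days before the effect window closes

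*Protocol article*

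**What the plan says.** All references are to the Protocol article. The Cost-effectiveness analysis section begins its costing with "Total medical costs over the 28-day follow-up period will be calculated" and lists intravenous and oral antibiotics, laboratory work and hospital days among the components. It then narrows one of them: "only costs of a readmission for a bacterial (re) infection, as defined in the outcome measures section, will be added to the analysis".

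The definition referred to stands under Primary outcome. It requires symptoms, abnormal temperature, raised inflammatory markers and antibiotics continued beyond 48–72 hours. Viral episodes in which antibiotics are never started, or are stopped within that time, are expressly not counted.

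For effects, "the CEA will look at the number of bacterial (re) infections within 28 days after finishing of antimicrobial therapy". Under Follow-up, "parents will receive a survey on day 7 and day 21", and lost productivity is one of the survey topics. The final outpatient visit is 28 days after treatment completion; no productivity questions are mentioned for it. Under Quality of life, the parents' questionnaire "collects information on total admission days and readmission rate, symptoms, side effects", together with the number of medical visits. No reason is given for restricting the readmission costs. Sensitivity analyses are promised where relevant, without saying on what.

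**The concern.** The economic case for an early oral switch rests largely on earlier discharge. The matching cost is an unplanned return to hospital, and infection is only one reason for such a return. An analysis that credits every hospital day saved, but debits only days caused by bacterial (re)infection, may record one side of the exchange more fully than the other.

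What is at stake is the incremental cost, the numerator of the final economic endpoint: "This ratio will be expressed as incremental costs per bacterial (re)infection avoided". Cost-effectiveness is a named secondary objective, and the Discussion expects a substantial cost reduction.

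The productivity surveys raise a second, separate issue. A (re)infection late in follow-up counts as an effect, while the working time that parents lose because of it may never be recorded.

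**Working it through.** The section states no unit cost, readmission rate or sample size of its own, so there is no economic figure to reproduce.

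**1. Which readmissions drop out.** Setting the costing rule beside the primary outcome definition, a readmission is costed only if it meets every element of that definition. Three kinds therefore add nothing: suspected infection with antibiotics stopped within 48–72 hours, viral illness handled in the same way, and any non-infectious cause such as side effects or feeding problems.

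**2. Whether the arms are treated alike.** Both arms receive 7 days of treatment (Intervention). Controls receive all of it intravenously, and their hospital days are a listed cost. An oral-arm infant switches after 48 to 72 hours and may go home once at least two oral doses are tolerated and the infant is clinically well (Follow-up). Suppose one infant in each arm has the same non-bacterial problem on day 5, with the oral-arm infant already discharged:

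- Control: still in hospital, so the day is costed.
- Oral arm: readmitted, so the day is not costed.

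In the treatment week the omission therefore runs one way, as long as controls stay in hospital for their course. After that week both groups can be at home, and the direction depends on readmission rates that the document does not give.

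**3. Illustrative size.** All inputs here are assumptions: an oral-arm excess of other readmissions of 1% to 10%, lasting 1 to 4 days each, against 3 to 5 hospital days saved per infant.

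Omitted bed-days per infant = excess rate × days per readmission

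- Low: 0.01 × 1 = 0.01; as a share of 5 days saved, 0.01 / 5 = 0.2%
- High: 0.10 × 4 = 0.40; as a share of 3 days saved, 0.40 / 3 = 13.3%

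For the omission to cancel the saving in bed-days, with 4-day stays and 3 days saved, the excess would have to be 3 / 4 = 75%.

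**4. Productivity window.** Effects end at 7 + 28 = day 35 from the start of therapy. The last survey is on day 21. The article does not say from when survey days are counted. The day-14 telephone call is dated from the start of antibiotics, so the same origin is the natural assumption.

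- Counted from start of therapy: 35 − 21 = 14 days uncovered, or 14 / 28 = 50% of the effect window.
- Counted from the end of therapy: 35 − (7 + 21) = 7 days uncovered, or 7 / 28 = 25%.

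**5. Medical-cost window.** The 28-day period has no stated start.

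- From the start of therapy: it ends on day 28, and 35 − 28 = 7 days of the effect window are not costed.
- From the end of therapy, read strictly: it ends on day 35, but the treatment-week costs listed in the same sentence fall outside it.
- Treatment week plus 28 days: it matches the effects exactly.

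**The case against.** The strongest reply is that the rule is the same for both arms. Control infants also go home, and their non-infectious readmissions are dropped too. Only a difference between arms biases the increment, and the document gives no rates by arm and no unit costs. Discharge also requires a clinically well infant who has tolerated oral doses, and severe hyperbilirubinaemia is an exclusion, which limits how many early returns to expect. This stands against any claim about size. It does not answer the treatment-week comparison, where identical wording gives unequal costing.

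Four stronger readings are tempting, and the document does not support them.

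- *The oral arm is shown to look cheaper.* The direction is plausible in the treatment week and unknown afterwards, so the text supports only that it may.
- *Most readmissions are ignored.* With an assumed all-cause rate of 3–8% against the planned 1%, the share left out would be 67–88%. That rate is not in the document, and a share pooled over both arms does not measure bias in the increment. With equal rates and similar costs the bias would be near zero.
- *The medical-cost window is mismatched.* Elsewhere the 28 days are counted after treatment, and treatment-week items are listed as costs, so a reading that matches the effects is available. This is an ambiguity.
- *The ratio is unusable.* At 1% with 275 per arm, the event counts tie with probability about 17.5%, and the ratio is then undefined. The plan provides for this with a dominance comparison and a bootstrapped cost-effectiveness plane, both of which can be reported when the effect difference is zero.

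It can also be said that sensitivity analysis is promised, that a condensed article may leave its content to a fuller document, and that the word introducing the cost list leaves room for outpatient and emergency visits. All of that is fair. The readmission restriction, however, is an explicit rule for the main analysis, and nothing in the article commits to relaxing it.

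**Conclusion.** The restriction on readmission costs is explicit, unexplained and capable of distorting the incremental cost. It may favour the oral arm, because control hospital days in the treatment week are costed whatever happens. The size cannot be derived from the document. On the assumed ranges it is about 0.2% to 13% of the bed-days saved, enough to affect the estimate but unlikely to reverse a saving.

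The productivity gap is firmer: about 14 days, half the effect window, if survey days run from the start of therapy, and still 7 days if they run from its end. The medical-cost window needs only a clear definition. These points concern a secondary economic objective and leave the primary non-inferiority comparison untouched.

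**What to change.** - Cost all-cause readmissions in both arms in the main analysis, and keep the version restricted to bacterial (re)infection as a named sensitivity analysis.
- Repeat the productivity questions at the final visit, covering the time since the last survey.
- State that costs run from the start of therapy to 28 days after its end, and give the origin from which survey days are counted.

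The cost is small. Resource use already comes from hospital databases, parents are already asked about admission days, readmissions and medical visits, and the final visit already exists. What is added is a change of wording and a few questions. The downside is more variance in costs per patient, since readmissions unrelated to treatment will enter; the restricted sensitivity analysis shows how much this matters. Reporting incremental cost ahead of the ratio is an optional matter of presentation.

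### The cost-effectiveness ratio divides by an infection difference that the trial plans as zero, so its sign and size are left to chance, and the stated fallback does not cover equal effect at lower cost

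*Protocol article*

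**What the plan says.** In the protocol article, the section Cost-effectiveness analysis sets the framework: "Following a superiority design, the cost-effectiveness analysis (CEA) will make a comparison between the intervention and the control group". The effect measure is the count of bacterial (re)infections in the 28 days after therapy, the same event as the primary outcome. A cost-effectiveness ratio is named as the final endpoint of this analysis: "This ratio will be expressed as incremental costs per bacterial (re)infection avoided". A fallback follows: "Otherwise, the CEA will focus on dominance of one treatment over the other with respect to lower cost and greater effect". Uncertainty in the ratio is to be illustrated with a bootstrapped cost-effectiveness plane, with sensitivity analyses where relevant.

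The section Power calculation rests on equal rates: "we assume a 1% infection rate (including new non-related infections) in both groups". Its result is as follows: "Based on a non-inferiority margin of 3% (minimum success rate 96%), 2×231 patients are needed". The error rates behind this figure are one-sided alpha 0.025 and 90% power. Enrolment is then raised: "we will include 2×275 neonates (total=550". The Discussion expects a substantial cost reduction from the oral switch.

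**The concern.** The result the trial is built to show is similar effect at lower cost, and neither stated economic summary fits it. A cost per infection avoided needs a difference in infections, which the design sets to zero. Dominance as worded needs a greater effect as well as a lower cost.

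The second objective is to quantify cost-effectiveness. If the endpoint stays as written, the headline figure would mostly reflect which arm happened to have one or two more infections. The cost difference, which the trial may estimate well, would be buried in the numerator of an unstable ratio.

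**Working it through.** **Inputs from the documents.** Infection rate 1% in each arm, margin 3 percentage points, power 90%, one-sided alpha 0.025, and 275 infants per arm (all from Power calculation); 1:1 allocation (Randomisation and blinding).

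**Input not in the documents.** The saving per infant with the oral switch. It is left as a symbol, S > 0.

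**1. The plan's own figure.** n per arm = 2 × 0.01 × 0.99 × (1.960 + 1.282)² / 0.03² = 231.16. This reproduces the stated 231 and confirms that the sample size assumes no difference between arms.

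**2. The denominator.** Its planned value is 0.01 − 0.01 = 0. Its standard error is √(2 × 0.01 × 0.99 / 275) = 0.0085, or 0.85 percentage points. One infection is 1/275 = 0.36 percentage points. Expected infections are 275 × 0.01 = 2.75 per arm.

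**3. How the counts fall.** The exact joint distribution of two independent binomial counts gives:

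| Per arm | Control rate | Oral rate | Equal counts (ratio undefined) | Oral fewer | Oral more |
|---|---|---|---|---|---|
| 275 | 1% | 1% | 17.5% | 41.2% | 41.2% |
| 231 | 1% | 1% | 19.2% | 40.4% | 40.4% |
| 275 | 0.5% | 0.5% | 25.6% | 37.2% | 37.2% |
| 275 | 2% | 2% | 12.3% | 43.9% | 43.9% |
| 275 | 1% | 0.5% | 16.6% | 66.4% | 16.9% |
| 275 | 1% | 2% | 9.1% | 12.2% | 78.7% |

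At 275 per arm and 1% in both arms, the counts differ by at most one in 49% of trials, by at most two in 73% and by at most three in 87%. The anticipated drop-out of 5% to 10% would leave about 248 to 261 per arm (275 × 0.90 and 275 × 0.95), between the first two rows.

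**4. What the ratio then says.** Let d be the number of infections avoided by the oral arm (control count minus oral count). The ratio is −S / (d/275) = −275·S/d.

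- d = +1: −275·S
- d = +2: −137.5·S
- d = +3: −91.7·S
- d = 0: undefined
- d = −1: +275·S

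Two things follow. Avoiding more infections makes the ratio smaller in size, so its magnitude does not rank results sensibly. When d is negative no infection is avoided: the figure is a saving per extra infection, and a larger value is better.

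**5. Bootstrap.** In 4,000 simulated trials at 1% in both arms, with 1,000 resamples each, the 95% bootstrap interval for the infection difference included zero in about 95% of trials. On average about 14% of the resamples had a difference of exactly zero, so the ratio could not be formed in them.

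**6. The fallback.** If the oral arm is cheaper, it meets the literal dominance condition only when it also has fewer infections: 41.2% of trials under equal true rates. It fails the condition in the other 59% (17.5% ties plus 41.2% with more infections). The cost half of the rule can be informative; the effect half rests on the same chance difference as the ratio.

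**The case against.** Four points are fair.

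- Equal 1% rates are a planning assumption, and an economic evaluation may estimate both differences without presuming equality. This stands as a limit on the figures: with a true difference the sign is less arbitrary, as the last two table rows show. Even so, 9% to 17% of trials would have tied counts.
- The bootstrapped plane needs no non-zero denominator and can show lower cost with an effect scattered around zero. This stands in part. The section offers the plane to illustrate uncertainty in the ratio and states no conclusion to be drawn from it for equal effect at lower cost.
- Per-patient total costs are already planned, so the cost difference will be available. That is true, and it makes the change cheap, but the article explicitly names the ratio as the endpoint. The point is about that choice, not about detail an article leaves out.
- Withholding dominance when the cheaper arm has more infections is correct. Agreed. The gap is the tie, and the reliance on a chance difference on either side of it.

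A reader might go further and infer that the ratio will usually be undefined. The documents do not support that: on the plan's inputs it can be computed in about 82% of trials. Nor is a dominance verdict ever undefined. Nor does one chance infection turn a dominant result into its reverse: from a one-infection lead, one event more or less at most produces a tie, and reversal needs a swing of two in the count difference.

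**Conclusion.** The point holds in a limited form. Under the trial's own planning assumption, the ratio named as the final economic endpoint has a true denominator of zero. It is exactly undefined in about 17.5% of trials (12% to 26% for common rates of 2% to 0.5%). Otherwise its sign and size are decided by chance, with fewer and more infections in the oral arm equally likely at 41% each. The fallback, read literally, does not cover equal effect at lower cost.

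These figures assume independent infants, 275 analysed per arm and equal true rates. The statements about the ratio's meaning also assume that the oral arm is cheaper, as the Discussion expects.

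It would be wrong to conclude that the economic analysis as a whole is uninformative: the costs, and the plane, can still be read. The matter concerns a secondary objective; the primary analysis and the sample size are unaffected.

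**What to change.** In the section Cost-effectiveness analysis:

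1. Replace the ratio as final endpoint with the mean cost difference per infant and its bootstrap 95% interval, reported beside the infection-rate difference and the non-inferiority result.
2. Add incremental net benefit, or an acceptability curve, over a stated range of values λ per infection avoided. Per infant this is λ·d/275 + S. It is defined at d = 0, and each infection moves it by a fixed λ/275.
3. Keep the cost-effectiveness plane.
4. Report the ratio only when the bootstrap cloud lies essentially in one quadrant, with the required share fixed in advance. At 1% in both arms this will seldom be met.

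No new data are needed. The cost is a change of wording, a little more analysis, a range for λ that has to be justified, and the loss of a single headline ratio.
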